#### Screening

The preliminary screening assesses sociodemographic variables (age, gender, employment relationship, insurance status) and information about various recruitment channels.

The German Version of the Patient Health Questionnaire (PHQ-9) [70] is administered as a depression screening inventory to detect subthreshold depression (PHQ-9 ≥ 5). The PHQ-9 consists of 9 items on a 4-point-scale with a rating scale ranging from 0 to 3 (0 = “not at all”, 1 = “several days”, 2 = “more than half the days”, 3 = “nearly every day”). Each item covers one symptom criterion domain of MDD. Additionally, an item is included to register severity of daily life limitations associated with depressive symptoms. The computerized version of the PHQ-9 (α = 0.88) shows an equally high internal consistency as the paper-pencil version (α = 0.89) [71]. Item 9 of BDI-II [72] will be applied to screen for suicidal ideation.

The Chronic Pain Grade Scale (CPG) [73] is applied to screen for chronic pain syndrome in combination with an additional item to measure chronicity of pain. The CPG grades pain severity by using the two dimensions “pain intensity” and “disability”. Severity of pain is categorized into the four hierarchical classes “Grade I” to “Grade IV”. The German Version of the CPG [74] showed overall a good internal consistency (α = .82). The German Version was adapted for this study to evaluate overall pain over the last 6 months.

## Outcome measurements

### Primary outcome

#### Depressive symptom severity at post-treatment (T1)

The primary outcome is depressive symptom severity at post-treatment (T1), assessed with the German Version of the Quick Inventory Depressive Symptomology (QIDS-SR16) [75]. The 16-item self-report inventory covers all nine DSM-5 symptom criterion domains of MDD. The QIDS-SR16 is characterized by high internal consistency of α = .86 [75]. The items are rated on a 4-point-scale ranging between 0 and 3. The total score ranges between 0 and 27, with a higher score indicating higher depressive symptom severity. Whereas a score between 0 and 5 indicates normal health status, scores between 6 and 10 indicate mild depressive symptomology, between 11 and 15 moderate, between 16 and 20 severe and scores greater than 20 indicate very severe depressive symptomology. Since the QIDS-SR16 is sensitive to symptom change and provides very similar results compared to longer clinical ratings like HAM-D17, HAM-D21, and HAM-D24 [75], this inventory will be administered to monitor changes in depressive symptom severity.

### Secondary outcomes

#### Depressive symptom severity at follow-up (T2 – T5)

Depressive symptom severity will be measured over a period of 36 months at 6-month (T2), 12-month (T3), 24-month (T4) and 36-month (T5) follow-up with QIDS-SR16.

#### Depression response

Clinical significance of depression response will be determined with QIDS-SR16 scores according to Jacobson and Truax [76].

#### Onset of clinical depression and bipolar disorder

Additionally, QIDS-SR16 will be used to classify participants regarding presence of clinical depression at all measurement points (T0-T5). A comparison of QIDS-SR16 scores to current and lifetime diagnosis based on Structured Clinical Interview for DSM-IV-TR Axis I Disorders (SCID) as measure criterion showed that QIDS-SR16 is a reliable screening instrument for diagnosis of clinical depression [77]. Cut-off scores of 13 and 14 yielded best results for sensitivity (76.5%) and specificity (81.8%) leading to correct classification of over 80% of participants [77]. For this study, a score ≥ 13 is defined as cut-off to identify possible cases of clinical depression for all measurement points within the 36-month follow-up period.

Further, Items adapted from the Composite International Diagnosis Interview version 3.0 (CIDI 3.0) and Screening Scales (CIDI-SC) [78], and the Epi-Q Screening Survey [79] as applied in the WHO World Mental Health Surveys International College Student Project [80] are used to assess presence of major depressive episode (MDE) and bipolar disorder (BPD) at all measurement points. Items recording onset and frequency of MDE and BPD episodes are included.

#### Perceived Stress

The 10-item version of the perceived stress scale (PSS-10) [81, 82] will be used to measure the perception of stress in participants. The scale particularly assesses how “unpredictable, uncontrollable, and overloading respondents find their lives” [83]. For the PSS-10 satisfactory internal consistencies from α = .78 to α = .91 were reported [83]. In a representative German community sample, a Cronbach’s alpha of .84 was reported for PSS-10 [84]. The PSS-10 was modified to address perception of stress load in the last week instead of the last month, because post-assessment (T1) is 9 weeks after randomization and duration of online-training lies between 6 to 8 weeks.

#### Insomnia Severity

Insomnia Severity will be measured using the Insomnia Severity Index (ISI) [85]. The ISI is a brief self-report scale composed of seven items to identify clinical insomnia. The questionnaire has been validated in clinical and community samples and is characterized by high internal consistency (α = 0.90 to 0.92) and adequate discriminative validity of the individual items [86, 87]. The German version of the ISI was examined in three cross-sectional studies in different target groups [88]. Cronbach’s Alpha was shown to be satisfactory in all three samples (α = .76 in adolescents, α = .77 in young adults, α = .81 in adult workers) [88].

#### Generalized Anxiety Disorder

The GAD-7 [89] will be used as a short self-report measure to assess likelihood of Generalized Anxiety Disorder. In the United States a high internal consistency of α = .92 was reported for the seven items of GAD-7. In a German sample, an internal consistency of α = .89 was found [90]. Overall, the GAD-7 is a valid and reliable instrument to screen for Generalized Anxiety Disorder [89, 90].

#### Panic and Agoraphobia

The severity of panic and agoraphobic symptoms will be assessed with the self-report version of the panic and agoraphobia scale (PAS) [91, 92]. The 13-item scale comprises five subscales, assessing panic attacks, agoraphobic avoidance, anticipatory anxiety, daily life limitations and health concerns. Additionally, the PAS contains an extra item for assessing unexpectedness versus expectedness of panic attacks, which is not included in the calculation of the total score [91]. The PAS was found to have a high internal consistency of α = .88 [91].

#### Pain intensity and pain associated disability

Assessment instruments for measurement of pain intensity and pain associated disability were selected under consideration of the recommendations of the Initiative on Methods, Measurement and Pain Assessment in Clinical Trials (IMMPACT) [93, 94].

The Multidimensional Pain Interference Scale (MPI) [95, 96] is administered to measure the degree of pain-associated disability regarding all-day activities. The German version of the MPI consists of 10 items rated on a 7-point scale. The MPI is characterized by excellent internal consistency (Cronbach’s alpha = .94) and good retest reliability (r = .78). Additionally, pain intensity will be recorded using an 11-point numerical rating scale from 0 (“no pain”) to 10 (“pain as bad as you can imagine”). This scale will be applied to rate the worst, least, average and current pain participants experienced during the last seven days.

#### Alcohol consumption

The Alcohol Use Disorder Identification Test (AUDIT) [97] will be applied to screen for harmful alcohol use. The AUDIT has been validated in six different countries and therefore is cross-nationally applicable [98, 99]. The 10-item self-report questionnaire measures a unidimensional construct with adequate internal consistency ranging between α = .8 and α = .83 [100, 101]. Validation of the AUDIT in a German general practice sample showed high retest reliability (ICC = .95) and adequate validity [102]. In the present study, the German Münster Version of the AUDIT following S3 guideline was applied (http://auditscreen.org/cmsb/uploads/audit-german-m-nster.pdf).

#### Emotional Exhaustion

Emotional exhaustion as the basic dimension of the burnout construct will be measured with a subscale of the Maslach Burnout Inventory (MBI-GS) [103]. In the present study, a German translation by Cillien and colleagues (2006) [104] was used. The 5-item subscale was applied to assess emotional exhaustion.

#### Quality of Life

Health-related quality of life will be assessed with the self-report questionnaireassessment of Quality of Life (AQoL-8D). This questionnaire consists of 35 items, covering the three physical dimensions “independent living”, “pain”, and “senses”, as well as the five psycho-social dimensions “mental health”, “happiness”, “coping”, “relationships”, and “self-worth” [105]. The AQoL-8D is characterised by a high Cronbach’s Alpha of 0.96 and good psychometric properties [105] and will be applied for cost-utility analyses.

#### Work capacity

Work capacity will be measured with the German version of the Subjective Prognostic Employment Scale (SPE) [106]. The SPE is a validated short self-report scale composed of 3 items with high internal consistency (Guttman scaling: rep = .99) for assessment of subjective endangerment and prognosis of work capacity [106].

### Cost measures

The provider (GET.ON institute) will provide information about the intervention costs, including costs pertaining initial phone calls by psychologists, documentation and coaching (e.g. individual written feedback) provided by qualified psychologists, technical support, server for hosting the interventions and overhead. Cost evaluation will be based on the German version of the Dutch cost questionnaire “Trimbos Institute and Institute of Medical Technology Questionnaire for Costs Associated with Psychiatric Illness” (TiC-P) [68]. In this self-report questionnaire, the usage of health care services (e.g. general practice services, intake of medications, sessions with psychotherapists or psychiatrists) and productivity loss (e.g. hospital days, absenteeism, presentism) is assessed. We will follow the human capital approach to value productivity losses [107]. The questionnaire was specifically adapted to the population of agriculturists, forester and horticulturists. A list of unit cost prices will be used to compute the total health care costs on a per-participant basis [108].

### Intervention-related outcomes

#### Experience of Working and Technological Alliances

The short version of the Working Alliance Inventory (WAI-SR) [109] will be applied to measure the therapeutic alliance between client and e-coach. The 12-item self-report questionnaire covers the three subscales a) agreement on tasks, b) agreement on goals and c) development of an affective bond. For the German Version, internal consistencies between α = .81 and α = .91 were reported for the subscales and internal consistencies between α = .90 and α = .93 for the total score [109, 110]. Participants in IG will complete the WAI-SR at T1 and T3. Additionally, e-coaches will be requested to complete the 10-item therapist version (WAI-SRT, developed by Adam O. Horvath, http://wai.profhorvath.com/) at T1 and T3. This will allow us to compare how the therapeutic relationship is experienced by client and by e-coach, to gain a differentiated and comprehensive picture of the experienced working alliance. The WAI-SR and the WAI-SRT were adapted in wording for the current study investigating therapeutic alliance in guided IMIs. The items were changed to refer to e-coaches instead of therapists and to online-trainings instead of therapy. Additionally, the Technological Alliance Inventory - Online Therapy (TAI-OT) will be administered to assess the technological alliance between client and the online-intervention. The TAI-OT is a new self-report questionnaire developed by Labpsitec (http://www.labpsitec.uji.es/esp/index.php) consisting of 12 items and measures the degree to which the online-program is perceived as helpful in achieving therapeutic goals.

#### Intervention satisfaction

Intervention satisfaction will be assessed using a German Version of the Client Satisfaction Questionnaire (CSQ-8 [111]; German Version: ZUF-8 [112]), specifically adapted for assessing patient satisfaction with IMIs (CSQ-I) [113]. The CSQ-8 is a self-report questionnaire consisting of 8 items characterised by high internal consistency (α = 0.93) [111]. The adapted German version CSQ-I has been validated for the assessment of patient satisfaction with IMIs and is characterised by equally high internal consistency [113]. CSQ-I will be applied to assess satisfaction with online-trainings in IG. An adapted version of the CSQ-I will be applied in CG to evaluate satisfaction with information material.

#### Side effects of psychotherapy

Side effects of psychotherapy will be assessed with the Inventory for the Assessment of Negative Effects of Psychotherapy (INEP). The INEP records whether any negative changes, which are experienced during or after the treatment in the social and/or work environment, are attributed on the psychotherapeutic intervention [114]. In this trial, an adapted 22-item version covering possible negative effects associated specifically with online-trainings (e.g. concerns about data protection) is applied.

Additionally, an open question will be included for qualitative assessments of negative side effects of IMIs. Participants will describe experienced negative events and side effects, their time of beginning, their frequency, and their duration. Two further questions rate the negative impact of these events in the past and at present time.

### Other assessments

#### Medical condition

Participants will be requested to visit a general practitioner and return a standardized formula for clarification of medical condition. This procedure is applied to ensure participants suffering from severe medical conditions receive appropriate medical care. Since the aim of the present study is to evaluate effectiveness (not efficacy) of online-trainings in standard care, the GP visit as well as the return of the formula is left to the responsibility of the participant. Further, the presence of diabetes mellitus will be assessed using a self-report item as part of the psycho-diagnostic assessment for the IMI program.

#### Covariates

As potential moderating variables, demographic information (e.g. gender, age, education), information about the agricultural farm (e.g. farm size, area cultivated, number of workers), and about the situation of the entrepreneurial family (e.g. financial situation, number of relatives living and working together, general work load) will be recorded at baseline. Further, a variety of predictors (e.g. personality, prior experience of violence and aggression, childhood experiences) will be included to assess relevant factors for development of depressive symptomology.

### Procedure on suicidal ideations

Suicidal ideation will be screened using PHQ-9 in screening assessment and QIDS-SR16 for further assessment points (T0-T5). A score ≥ 1 on suicide item of PHQ-9 (“Thoughts that you would be better off dead or of hurting yourself in some way?”) or QIDS-SR16 (QIDS-SR16 Item = 1: “I feel that life is empty or wonder if it’s worth living”, QIDS-SR16 Item = 2: “I think of suicide or death several times a week for several minutes”, QIDS-SR16 Item = 3: “I think of suicide or death several times a day in some detail, or I have made specific plans for suicide or have actually tried to take my life”), leads to BDI-II suicide item [72]. A score ≥ 1 on BDI-II suicide item results in a standardized suicide protocol adapted from prior trials [115, 116].

Participants receive an online information letter with detailed information on available health services and the advice to seek professional help if symptoms increase. The wording of the online information letter is adapted in emphasis, depending on the severity of the indicated suicidality (BDI-II Item = 1: “I have thoughts of killing myself, but I would not carry them out”, BDI-II Item = 2: “I would like to kill myself”, BDI-II-Item = 3: “I would kill myself if I had the chance”). This procedure will be administered on all assessment points and independent of study inclusion.

Eligible participants will be asked to return a signed non-suicide contract as part of screening and baseline (T0), if they are able to distance themselves from suicidal ideation. Participants are informed that the IMI program is not provided as intervention for problems accompanied by persisting suicidal ideation.

For BDI > 1, a detailed clarification of self-endangerment will be performed for all screened participants independent of study inclusion status and assessment point. A telephone contact will be announced via e-mail in case of not returning a given text module or sending an informal answer in response to the online information letter within 48 h of undergoing the assessment point. If self-endangerment remains unclear, psychotherapists (at least) in training will contact the participant via telephone and initiate further actions. Further actions will be determined depending on perceived endangerment. If participant remains not contactable for further 48 h, the police department will be informed. All steps are closely monitored and supervised by a licenced psychological psychotherapist.

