### Intervention

#### Intervention condition

Participants in the intervention group (IG) will be transferred to the service provider GET.ON to get access to a tailored and guided IMI program with the option of conducting one of six available IMIs. The IMI program consists of a 3-step intervention entailing (1) *psycho-diagnostic assessment*, (2) *participatory selection of a suitable (guided) IMI* and (3) *access to IMI*. The IMI program will be carried out by the external service company GET.ON without involvement from the study team. Thus, the GET.ON institute is responsible for providing an adequate care of the participants against the background of the psycho-diagnostic assessment and the information they receive in the course of patient contact. This includes for example the handling of adverse events in the course of e-coaching. The study team evaluates in this setting the standard procedure of the GET.ON institute for the allocation of the different trainings and the treatment of participants in the course of the IMI program.
The *psycho-diagnostic assessment* is based on a selection of self-report questionnaires measured as part of baseline assessment (T0). Relevant baseline assessment values are transmitted electronically to GET.ON for each participant to allow for psycho-diagnostic assessment based on allocation rules applied in supply routine of GET.ON. Each participant is assigned to a personal e-coach after signing in to the intervention platform. E-coaches are trained psychologists, who are in training for a further qualification in psychotherapy and supervised by an experienced psychological therapist.Participants are contacted via telephone or private message function on the intervention platform by their personal e-coach for *participatory selection of a suitable (guided) IMI.*

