The IMIs are accessible on an online-based intervention platform via either computer (e.g. desktop PC, laptop) or mobile device (e.g. tablet, smartphone). The IMIs contain psycho-educative text material, exercises, and testimonials of exemplary personas, who accompany the participants throughout the intervention. Additionally, interactive elements in form of auditory material and videos clips are included. Audio clips for example are used to convey relaxation techniques, while video clips often serve to give a comprehensible overview about theoretical concepts by experts. Since a focal point is the transfer of content and strategies learned into every-day life, many application examples, instructions and exercises, as well as homework assignments for practising between lessons are included. The content of the online-trainings has been specifically adapted to the target population by inclusion of fitting picture and video material, as well as exemplary testimonials and fictional personas living and working in the agricultural setting. These personas describe the struggle with everyday problems and challenges in green professions, e.g. generational conflicts or handing over of the company to the younger generation.

Subsequent to the completion of the IMI, participants are followed up for 12 months by their individual e-coach to consolidate the treatment effect. During this phase, participants are contacted once a month through telephone or the internal messaging system by their personal e-coach to review their current state, report problems, and give account regarding the transfer of strategies learned into the daily routine.

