### Assessments

All assessments will be conducted online. For an overview of instruments at screening, baseline (T0), post-treatment (T1), and follow-up assessments (T2-T5), see Table 1. Participants will receive 10€ for completion of each follow-up assessment, starting with T1.

**Table 1 Tab1:** Overview of the assessments

Instruments	Aim	Time of measurement						
		Screening	T0	T1	T2	T3	T4	T5
Screening Instruments								
PHQ-9	Patient Health Questionnaire	✔						
CPG	Chronic Pain Grade Questionnaire	✔						
Chronicity of Pain	Pain longer for 6 months (yes/no)	✔						
Primary Outcome								
QIDS-SR16	Quick Inventory for Depressive Symptomatology		✔	✔^a^	✔	✔	✔	✔
Secondary Outcomes								
Adapted items from CIDI 3.0, CIDI-SC, and Epi-Q Screening Survey	Prevalence of major depression and bipolar disorder		✔	✔	✔	✔	✔	✔
PSS-10	Perceived Stress Scale		✔	✔	✔	✔	✔	✔
ISI	Insomnia Severity Index		✔	✔	✔	✔	✔	✔
GAD-7	Generalized Anxiety Disorder		✔	✔	✔	✔	✔	✔
PAS	Panic and Agoraphobia Scale		✔	✔	✔	✔	✔	✔
MPI	Multidimensional Pain Inventory		✔	✔	✔	✔	✔	✔
NRS	Pain Intensity (0–10)		✔	✔	✔	✔	✔	✔
AUDIT-10	Alcohol use disorder identification test		✔	✔	✔	✔	✔	✔
MBI-GS	Maslach-Burnout-Inventory (subscale emotional exhaustion)		✔	✔		✔		
AQoL-8D	Quality of life		✔	✔	✔	✔	✔	✔
SPE	Subjective prognosis of employment		✔	✔	✔	✔	✔	✔
Cost measurement								
TiC-P	Utilisation of health services, work-related productivity		✔	✔	✔	✔	✔	✔
Intervention-related Outcomes								
WAI-SR^b^, WAI-SRT^c^	Therapeutic relationship			✔		✔		
TAI-OT^b^	Technological alliance			✔	✔			
CSQ-I	Patient satisfaction			✔				
INEP^b^	Inventory of negative effects in psychotherapy			✔	✔	✔		
Negative effects^b^	Negative effects in psychotherapy			✔	✔	✔		
Other assessments								
Other questions	Socio-demographics		✔					
	Predictors for development of major depression		✔					
Diabetes	Diabetes diagnosis (yes/no)		✔					
BDI-II	Suicidality-Item	✔	✔	✔	✔	✔	✔	✔

^a^Primary outcome is the standardized mean difference between intervention and control group at T1. QIDS-SR16 will also be assessed at T0 and T2-T5

^b^Recorded in intervention group only

^c^Recorded in e-coaches only

*T0* Baseline, *T1* 9 weeks, *T2* 6 months, *T3* 12 months, *T4* 24 months, *T5* 36 months

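### At T1 to T5, a QIDS-SR16 suicide answer of 3 leads to no stated safety step when the BDI-II suicide item is 0

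*Protocol article*

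**What the plan says.** The section Procedure on suicidal ideations in the Protocol article sets out a two-stage screen. From T0 to T5 the first stage is the QIDS-SR16 suicide item, and an answer of 1 or more brings up the BDI-II suicide item. The printed text of QIDS-SR16 answer 3 covers thoughts about death or suicide that occur "several times a day in some detail, or I have made specific plans for suicide or have actually tried to take my life".

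The second stage then governs: "A score ≥ 1 on BDI-II suicide item results in a standardized suicide protocol". The first element described is an online letter, with wording graded for BDI-II scores 1, 2 and 3. The next threshold is higher: "For BDI > 1, a detailed clarification of self-endangerment will be performed for all screened participants independent of study inclusion status and assessment point". The same paragraph continues: "A telephone contact will be announced via e-mail in case of not returning a given text module", with a 48-hour limit. A call by a psychotherapist follows if the danger remains unclear, and the police are informed if the person cannot be reached for a further 48 hours. The section closes with a supervision statement: "All steps are closely monitored and supervised by a licenced psychological psychotherapist".

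At screening and T0 there is an additional measure. Eligible people are asked for a signed non-suicide contract, and inability to sign is an exclusion criterion (Inclusion and exclusion criteria). No such contract is stated for T1 to T5.

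**The concern.** The QIDS-SR16 score is used once, as a threshold of 1 or more, and then not again. A participant who feels life is empty and one who reports a plan or an attempt are sent to the same second item, and that item alone decides what follows. If the second answer is 0, the most severe first answer leads to no stated check.

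Several features of this trial make that worth closing. All assessments are online, so no face-to-face visit is stated at which a discordant pair of answers might be noticed. The Discussion says that no upper limit of depression severity was set and that cases of manifest depression may be included. The Background cites raised suicide risk in the agricultural sector in several countries. Controls have usual care and information links, which are passive safeguards.

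**Working it through.** No figure in the plan is in dispute. The check traces the printed rule and then the dates, to see which assessments a change could still reach.

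**1. Stated action at T1 to T5 after a QIDS-SR16 suicide answer of 3**

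| BDI-II item | Suicide protocol opened? | Clarification stated? |
|---|---|---|
| 0 | No | No |
| 1 | Yes (letter; further steps not shown) | Not clearly |
| 2 | Yes | Yes |
| 3 | Yes | Yes |

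Only the first row leaves the participant outside the protocol altogether. The table counts answer categories and says nothing about how often each occurs.

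**2. Does the second item re-ask the first?** QIDS-SR16 answer 3 covers frequent detailed thoughts, a plan or an attempt. The printed BDI-II levels describe thoughts that would not be acted on (1), a wish (2), and intent given the chance (3). None names a plan or a past attempt. A person could answer 3 on the first item because of an attempt and then answer the second by present wish or intent. The wording of BDI-II answer 0 is not printed.

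**3. Other stated safeguards**
- Supervision covers the steps that are taken, so it does not create one at BDI-II 0.
- Provider responsibility ("This includes for example the handling of adverse events in the course of e-coaching") applies to the intervention arm only and is not tied to either score.
- After the training, "participants are followed up for 12 months by their individual e-coach to consolidate the treatment effect". Training of 6 to 8 weeks is about 1.4 to 1.8 months, and adding 12 months gives 13.4 to 13.8 months. T4 is at 24 months, so neither arm has stated coach contact at T4 or T5. Pace may vary, but the training itself would have to last about 24 − 12 = 12 months for contact to reach T4.

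**4. Which assessments could an amendment still reach?** Inputs: recruitment January 2018 to April 2019 (Trial status) and publication on 9 September 2019. Assumptions: enrolment from 1 January 2018 to 30 April 2019, which is 365 + 120 = 485 days; uniform accrual, since accrual is not reported; no delay in making the amendment.
- T1: the last is due 30 April 2019 + 9 weeks = 2 July 2019, which is 69 days before publication. None remain.
- T2: those enrolled after 9 March 2019, 22 + 30 = 52 days; 52/485 = 11%. The last are due about October 2019.
- T3: those enrolled after 9 September 2018, 113 + 120 = 233 days; 233/485 = 48%. The last are due about April 2020.
- T4: all, January 2020 to April 2021.
- T5: all, January 2021 to April 2022.

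**The case against.** The strongest reply is that a journal article only summarises the suicide procedure. The standardized protocol adapted from earlier trials is not shown, and handling of discordant answers could sit there. That holds for steps inside the protocol. It does not answer the case at BDI-II 0, because the article states the entry condition, and a score of 0 does not meet it. Unseen steps cannot, on the printed rule, reach someone who never enters. A fuller operating procedure could still contain a separate QIDS-SR16 trigger, so the point is confined to the rule as printed.

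A second reply is that a broad first item followed by one graded by wish and intent is a reasonable design, and that QIDS-SR16 answer 3 can reflect frequent thoughts of death without intent. This is fair, and it is why the point is an improvement and not an error. It is weaker for a reported plan or attempt.

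Two stronger readings should be resisted. A reader might infer that QIDS-SR16 answer 3 with BDI-II 1 brings only a letter. The documents do not establish that: the unseen protocol may add steps at BDI-II 1, and the telephone step depends on not answering the letter, which everyone at BDI-II 1 or more receives, although its paragraph opens with the higher threshold. A reader might also extend the gap to T0. There the request for a non-suicide contract names no BDI-II score and could, read literally, also cover a score of 0.

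**Conclusion.** The point holds for one combination at T1 to T5: QIDS-SR16 suicide answer 3 with BDI-II item 0. As printed, no letter, clarification or contact follows. The rule is stated and gives a poor safety result in that case, so this is more than detail left out of an article.

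The size in participants cannot be derived. The combination is probably rare, and its plausibility depends partly on the unprinted wording of BDI-II answer 0. The primary outcome, sample size and analysis are not affected. The case for acting rests on the seriousness of a reported plan or attempt and on how little the change costs. Confidence is medium, because the full suicide protocol is not available.

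**What to change.** By a short amendment, at all remaining assessment points and in both arms, start the existing clarification of self-endangerment when the BDI-II item is above 1 or the QIDS-SR16 suicide item equals 3, whatever the BDI-II answer. Because that pathway begins with a reply to the online letter, the new trigger should release the letter as well.

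No new question is needed. Table 1 already lists the BDI-II suicidality item at T0 to T5. The QIDS-SR16 is the T1 outcome measure, and the table's footnote adds that "QIDS-SR16 will also be assessed at T0 and T2-T5". The work is one added condition in the online survey, using the psychotherapists already in place.

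The downside is a few more contacts, some of them false alarms such as frequent thoughts without intent. Most should end with a text reply within 48 hours, but in rare cases a participant who cannot be reached could be escalated as far as the police step. Setting the threshold at 3 is a judgement: that is the answer whose text includes plans or an attempt, and a lower threshold would raise the number of false alarms.
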